### **7.2.9 Device Usage Specifications**

The sponsor will provide the "Instructions for Use" and the investigator's brochure for reference. Training will be conducted during the trial preparation phase to ensure all trial personnel are proficient in using the trial device.

### **7.3 Monitoring Plan**

**7.3.1 Clinical Trial Preparation:** Before subject enrollment, the monitor will assist the investigator in submitting materials to the ethics committee, obtaining approval, signing the trial agreement, and completing provincial drug regulatory agency filing.

**7.3.2 Initiation Training:** All personnel involved in the trial will receive project training to ensure familiarity with GCP and protocol requirements, device operation, and clear division of responsibilities.

**7.3.3 Monitoring Visits:** The monitor will verify the informed consent process, inclusion/exclusion criteria, and protocol compliance. On-site monitoring visits will include:

**7.3.3.1** Ensuring the informed consent process is standardized.

**7.3.3.2** Verifying compliance with inclusion/exclusion criteria.

**7.3.3.3** Checking for protocol deviations and ensuring deviations are recorded and reported.

**7.3.3.4** Ensuring original records are timely, complete, accurate, and truthful.

**7.3.3.5** Verifying timely and complete eCRF completion and ensuring data accuracy.

**7.3.3.6** Ensuring trial product distribution, usage, and recovery records are complete and accurate.

**7.3.3.7** Recording adverse events and ensuring serious adverse events are reported as required.

**7.3.3.8** Reporting device defects as required.

### **7.3.3.9 Ensuring subject rights are protected as per the informed consent form.**

If issues are found, they will be recorded, and the investigator will be warned and provided with targeted training. The monitor will assist the trial site in rectifying issues. A monitoring visit report will be submitted to the sponsor and the principal investigator after each visit.

**7.3.4 Regular Quality Control:** Quality control personnel will periodically review the work of each center, generate quality control reports, and follow up until issues are resolved. Monitors will regularly coordinate with the quality control of clinical trial institutions and the audits conducted by the sponsor, and address any identified issues through corrective actions.

## **8. Statistical Considerations**

### **8.1 Statistical Design, Methods, and Analytical Procedures**

#### **8.1.1 Statistical Software and General Requirements**

**Software:** SAS software (version 9.4 or above) will be used for analysis.

**Descriptive Statistics:** For continuous variables, descriptive statistics will include the number of cases, mean, standard deviation, quartiles, minimum, and maximum values. For categorical variables, descriptive statistics will include frequency and percentage.

**Detailed Statistical Methods:** A comprehensive statistical analysis plan (SAP) will be developed and provided separately.

#### **8.1.2 Case Entry Analysis**

The total number of cases, as well as the number of cases selected and completed at each center, will be listed to determine three analytical data sets: Full Analysis Set (FAS), Per Protocol Set (PPS), and Safety Set (SS). A detailed classification of these data sets will be provided in the SAP.

#### **8.1.3 Demographic Data and Baseline Analysis**

Descriptive statistics for demographic data and other baseline characteristics will be presented as follows:

For continuous variables: number of cases, mean, standard deviation, quartiles, minimum, and maximum values.

For count and grade data: frequency and composition ratio.

Inferences (P values) will be listed as descriptive results.

#### **8.1.4 Analysis of the Primary Endpoint**

#### **8.1.5 Analysis of the Primary Efficacy Endpoints**

The success rate of valve repair with a prosthetic ring at 6 months post-surgery will be compared using the Newcombe method or Fisher's exact test to evaluate differences between groups. The Newcombe method will be used to calculate the two-sided 95% confidence interval (CI) for the rate difference between the experimental group and the control group. Non-inferiority will be assessed based on a non-inferiority boundary value of -10%. Both PPS and FAS analyses will be conducted.

#### **8.1.6 Analysis of Secondary Endpoints**

##### **8.1.6.1 Analysis of Secondary Efficacy Endpoints**

**8.1.6.1.1** Echocardiographic assessment of valve regurgitation severity at discharge or 30 days, 3 months, 6 months, and 12 months post-surgery will be compared between groups using the Cochran-Mantel-Haenszel (CMH) test.

**8.1.6.1.2** Changes in echocardiographic parameters (right atrial size, right ventricular size, radial value, width of the narrowest part of the regurgitant beam, and area of reverse blood flow) at discharge or 30 days, 3 months, 6 months, and 12 months post-surgery will be compared using the t-test.

**8.1.6.1.3** NYHA cardiac function classification at discharge or 30 days, 3 months, 6 months, and 12 months post-surgery will be compared between groups using the CMH chi-square test or rank-sum test.

**8.1.6.1.4** The risk of reoperative tricuspid valve surgery, performance of the test instrument, and success rate of the surgical technique due to tricuspid valve insufficiency will be compared using the chi-square test or Fisher's exact test.

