#### **7.1.2.2 Rationale for Randomized Controlled Design**

The randomized controlled trial (RCT) design is chosen because it provides a high level of reliable evidence in clinical research. In this trial, participants who meet the inclusion criteria will be randomly assigned to one of two groups:

Test Group: Participants will receive the trial Annuloplasty Ring.

Control Group: Participants will receive a commercially available Annuloplasty Ring (manufactured by Edwards, which has been approved by the National Medical Products Administration (NMPA). This control device is widely used in clinical practice and has a well-established efficacy profile. Random assignment ensures balanced and comparable groups, minimizing bias and enhancing the reliability of the results.

Dynamic Randomization: The trial uses a dynamic randomization method, taking into account two key factors:

Study Center: Ensures balanced distribution across multiple sites.

Severity of Regurgitation: Participants are stratified based on the degree of valve leakage (mild, moderate, or severe).

Central Randomization System: The trial employs a Clinical Trial Central Randomization System (DAS for IWRS) to allocate random numbers, ensuring fairness and transparency in group assignment.

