**7.1.8.4.7 Thromboembolic events related to the trial device.**

**7.1.8.5 Device defects.**

**7.1.8.6 Other adverse events.**

## **7.2 Trial Procedures**

### **7.2.1 Screening (within 30 days preoperatively)**

**7.2.1.1** Patients must sign the informed consent form before screening.

**7.2.1.2** Collect demographic data (gender, date of birth, weight, and height).

**7.2.1.3** NYHA functional class, vital signs (blood pressure, pulse).

**7.2.1.4** Laboratory tests: Complete blood count, blood biochemistry, coagulation function, and pregnancy test if necessary.

**7.2.1.5** Electrocardiogram (ECG), echocardiography (TTE or TEE).

**7.2.1.6** Record antiplatelet or anticoagulant medications.

**7.2.1.7** Randomization using a central randomization system.

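### Section 8.1.6.1.2 fixes an unadjusted t-test on echo changes: valid, but less precise than an ANCOVA on the preoperative value and the randomisation factors

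*Protocol*

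**What the plan says.** Section 8.1.6.1.2 defines the outcome as "Changes in echocardiographic parameters (right atrial size, right ventricular size, radial value, width of the narrowest part of the regurgitant beam", together with reverse-flow area. At discharge or 30 days and at 3, 6 and "12 months post-surgery will be compared using the t-test". It names no covariate and no stratum. Unlike 8.1.6.1.1 and 8.1.6.1.3, it does not state that the comparison is between groups, although that is the natural reading.

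The information for adjustment should already be there. Section 7.2.1 lists "Electrocardiogram (ECG), echocardiography (TTE or TEE") at screening. Section 7.1.2.2 describes dynamic randomisation on two factors: "Study Center: Ensures balanced distribution across multiple sites", and severity, where "Participants are stratified based on the degree of valve leakage (mild, moderate, or severe").

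Section 8.1.1 leaves detailed methods to a separate SAP, which was not available for this review. The t-test itself is not left to the SAP; the protocol names it.

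**The concern.** A t-test on change subtracts the whole baseline value, which is the same as fixing the regression slope of follow-up on baseline at 1. The true slope is usually below 1, and then the subtraction adds noise. ANCOVA estimates the slope from the data and, in large samples, is never less precise. A test that also ignores factors used to balance the allocation has a standard error that takes no credit for that balance.

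These comparisons are the trial's evidence on right-heart size and on residual regurgitation as a continuous measure, with about 75 evaluable patients per arm. The aim is to show comparability with a marketed ring. In that setting an imprecise comparison is not harmless, because a non-significant P value is easily read as no difference.

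**Working it through.** **Inputs from the protocol**
- Sample size (8.2.1): 75 per arm required, 82 per arm enrolled; dropout about 10% (8.4).
- Two-sided tests at 0.05 (8.3).
- Balancing factors: centre and severity (7.1.2.2).

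**Assumed, because the protocol gives no figure:** the SDs of the echo parameters and the baseline/follow-up correlation ρ.

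**Step 1. The plan's own figure.** The protocol gives no calculation for the secondary tests, so only the primary sample size can be reproduced. With 95% in both arms, a margin of 10 points, one-sided 0.025 and 80% power:

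n = (1.960 + 0.842)² × 2 × 0.95 × 0.05 / 0.10² = 7.85 × 0.095 / 0.01 ≈ 74.6, so 75 per arm.

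This matches. With 82 enrolled and 10% lost, 82 × 0.9 = 73.8 remain, so 75 per arm is a fair working number below.

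**Step 2. Equal SDs (s).** Per-patient variances:
- Change score: 2s²(1 − ρ)
- ANCOVA: s²(1 − ρ²)
- Ratio, ANCOVA to change score: (1 + ρ)/2

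The interval width scales with the square root of the ratio. The equivalent increase in patients is 1/ratio − 1. The difference detectable with 80% power is 2.80 × √(2/75) = 0.457, times the per-patient SD.

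| ρ | Variance ratio | Variance saved | Interval narrower by | Equivalent extra patients | Detectable difference, t-test → ANCOVA (SD units) | t-test power where ANCOVA has 80% |
|---|---|---|---|---|---|---|
| 0.2 | 0.60 | 40% | 23% | 67% | 0.58 → 0.45 | 58% |
| 0.3 | 0.65 | 35% | 19% | 54% | 0.54 → 0.44 | 62% |
| 0.5 | 0.75 | 25% | 13% | 33% | 0.46 → 0.40 | 68% |
| 0.7 | 0.85 | 15% | 8% | 18% | 0.35 → 0.33 | 73% |
| 0.9 | 0.95 | 5% | 3% | 5% | 0.205 → 0.199 | 78% |

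**Step 3. Unequal SDs.** Section 4.2 cites a study of the control ring in 136 patients, with regurgitation percentage falling from 40.0 ± 16.6% to 11.8 ± 10.3%. Read ± as an SD and let k = follow-up SD / baseline SD = 10.3/16.6 = 0.62. The variance ratio becomes

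k²(1 − ρ²) / (1 + k² − 2ρk).

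Its maximum over ρ is at ρ = k and equals k² = 0.385. So, whatever the correlation, ANCOVA would save at least 61% of the variance, and intervals would be at least 38% narrower. Unless ρ exceeds 16.6/(2 × 10.3) = 0.81, the change score is noisier than the follow-up value alone. This is one cited study of a measure close to, but not the same as, reverse-flow area. Chamber sizes may lie nearer the equal-SD case.

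**Step 4. Validity of the t-test.** A simulation used 150 patients, three severity strata, allocation balanced on severity, baseline correlated 0.6 with severity, and 3,000 runs per setting.

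| ρ | Type I error, t-test | Type I error, ANCOVA | Power at 0.4 SD, t-test | Power at 0.4 SD, ANCOVA with strata |
|---|---|---|---|---|
| 0.3 | 0.040 | 0.051 | 0.52 | 0.71 |
| 0.5 | 0.038 | 0.043 | 0.69 | 0.81 |
| 0.7 | 0.046 | 0.047 | 0.88 | 0.92 |

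The t-test is at or slightly below its nominal 0.05; it is not inflated. Severity acted on follow-up only through baseline, and centre was not simulated. The power gain shown is therefore essentially that of baseline adjustment.

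**Step 5. What counts as change in diameter.** Section 7.1.2.3 measures annular increase against the preoperative value. Section 7.1.6.2.2 measures it against the 3-month value. Section 8.1.6.1.2 does not say which reference applies. A 3-month reference cannot serve the discharge and 3-month visits that 8.1.6.1.2 also lists.

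**The case against.** The strongest objection is that this is a choice between two acceptable methods on secondary endpoints. Section 8.5 judges the trial on the primary non-inferiority test alone, and nothing here alters that test, its sample size or its conclusion. That stands, and it keeps the point minor. It does not remove the point: the protocol names the less precise method, and the alternative uses data the trial should already hold.

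The size is also uncertain. Both ρ and equal SDs are assumptions. The protocol does not list which parameters are read at screening, and baseline may be TTE or TEE while follow-up is TTE.

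Four stronger readings are tempting, and the protocol does not support them:
- **That baseline is discarded.** The outcome is a change, so baseline enters by subtraction. It is used inefficiently.
- **That the comparison is biased.** Under randomisation, regression to the mean is expected equally in both arms, and chance imbalance adds variance rather than systematic error.
- **That the ordinal analyses throw away the severity strata.** Regurgitation grade "will be compared between groups using the Cochran-Mantel-Haenszel (CMH) test", a test that takes strata by construction. Naming them is ordinary SAP detail, and the unseen SAP may name severity or centre. For NYHA class, which "will be compared between groups using the CMH chi-square test or rank-sum test", the rank-sum option is unstratified, but the choice is left open. None of this is part of the finding.
- **That severity is the only factor at issue.** Centre is a balancing factor too.

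**Conclusion.** The point holds as a loss of precision on secondary endpoints. The t-test fixed in 8.1.6.1.2 is valid and at most mildly conservative. Under equal SDs and ρ of 0.3 to 0.7, baseline ANCOVA would have 35% to 15% less variance. The saving would be larger for any parameter whose spread shrinks after repair, and it falls to 5% at ρ = 0.9. The further gain from adding severity and centre was not quantified. The primary non-inferiority result is unaffected. This is an improvement at little cost and does not put the trial's conclusion in doubt.

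**What to change.** 1. Reconcile sections 7.1.2.3 and 7.1.6.2.2 on the reference point for annular diameter change, and state in 8.1.6.1.2 which one applies. A 3-month value is measured after randomisation and should not be used as the baseline covariate.
2. Replace the t-test in 8.1.6.1.2 with a between-group ANCOVA at each visit: follow-up value on arm, preoperative value of the same parameter, regurgitation-severity stratum and centre. Report the adjusted difference with its 95% interval.
3. Pool small centres by a rule set in advance. Section 7.1.5.4 allows up to 20 sites, which is many terms for about 150 evaluable patients.
4. Confirm that the screening eCRF records all five parameters.

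The cost is a wording change in the protocol, matching text in the SAP and a few lines of SAS. No extra visits or examinations are needed, provided the screening echo records the parameters.

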##### **8.1.6.2 Secondary Safety Endpoint Analysis**

**8.1.6.2.1** The incidence of device-related serious adverse events (SAEs) at discharge or 30 days, 3 months, 6 months, and 12 months post-surgery will be compared between groups using the chi-square test or Fisher's exact test.

**8.1.6.2.2** The incidence of all-cause mortality at discharge or 30 days, 3 months, 6 months, and 12 months post-surgery will be compared using the chi-square test or Fisher's exact test.

**8.1.6.2.3** The incidence of cardiovascular death related to the test device at discharge or 30 days, 3 months, 6 months, and 12 months post-surgery will be compared using the chi-square test or Fisher's exact test.

**8.1.6.2.4** The incidence of major bleeding related to the test device at discharge or 30 days, 3 months, 6 months, and 12 months post-surgery will be compared using the chi-square test or Fisher's exact test.

**8.1.6.2.5** The incidence of severe damage to cardiac or other body structures related to the test device at discharge or 30 days, 3 months, 6 months, and 12 months post-surgery will be compared using the chi-square test or Fisher's exact test.

**8.1.6.2.6** The incidence of device-related infective endocarditis at discharge or 30 days, 3 months, 6 months, and 12 months post-surgery will be compared using the chi-square test or Fisher's exact test.

**8.1.6.2.7** The incidence of thromboembolic events related to the test device at discharge or 30 days, 3 months, 6 months, and 12 months post-surgery will be compared using the chi-square test or Fisher's exact test.

**8.1.6.2.8** The incidence of adverse events from postoperative to 5-year follow-up will be compared using the chi-square test or Fisher's exact test.

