#### **7.1.7.1.2 Device defects.**

#### **7.1.7.1.3 Other adverse events.**

### **7.1.7.2 Methods and Timing for Evaluating, Recording, and Analyzing Safety Parameters**

**7.1.7.2.1** Serious adverse events related to the trial device are defined as events determined by the independent clinical event committee to be related, definitely related, or possibly related to the trial device, including:

- All-cause mortality: Cardiovascular and non-cardiovascular deaths from any cause.
- Cardiovascular death related to the trial device: Defined according to the Valve Academic Research Consortium (VARC) as death due to cardiac causes (e.g., myocardial infarction, cardiac tamponade, worsening heart failure), non-coronary vascular disease, surgery-related deaths (including deaths related to surgical complications or their treatment), sudden or unexplained deaths.
- Major bleeding related to the trial device: Defined according to the Bleeding Academic Research Consortium (BARC) as type 3b or higher bleeding (excluding type 4).

| Type | Explain |
|------|---------|
| 0    | NH      |

|                         |    |                                                                                                                                                                                                                                                                                                                                                                                                                          |
|-------------------------|----|--------------------------------------------------------------------------------------------------------------------------------------------------------------------------------------------------------------------------------------------------------------------------------------------------------------------------------------------------------------------------------------------------------------------------|
| 1                       |    | Non-active bleeding that does not result in a visit to a physician; may include bleeding that results in a patient discontinuing a medication without medical advice                                                                                                                                                                                                                                                     |

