| 5 Fatal bleeding        | 5a | Possible fatal bleeding; non-pathological or imaging basis but clinically suspicious                                                                                                                                                                                                                                                                                                                                     |
|                         | 5b | Determine the presence of fatal bleeding with obvious signs of bleeding or with pathological or imaging evidence                                                                                                                                                                                                                                                                                                         |

- Severe damage to cardiac or other body structures related to the trial device.
- Infective endocarditis related to the trial device.
- Thromboembolic events related to the trial device: Defined as myocardial

infarction, cerebral infarction, or organ embolism caused by thrombosis, with clinical or imaging evidence of arterial occlusion.

**7.1.7.2.2** Surgical details and intraoperative complications will be recorded in the electronic case report form (eCRF). Safety evaluations will be conducted at discharge/30 days, 3 months, 6 months, 12 months, and annually from 2 to 5 years postoperatively, recording all adverse events. All eCRF data will be submitted to the statistical center for clinical data analysis and evaluation.

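### Six of the eight between-arm safety tests count only events judged device-related; the same harms should also be compared on all events meeting the definition, regardless of attribution.

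*Protocol*

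**What the plan says.** Protocol section 8.1.6.2 names eight between-arm safety tests, all by chi-square or Fisher's exact test. Six are limited to device-related events:

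- serious adverse events (8.1.6.2.1);
- cardiovascular death (8.1.6.2.3);
- major bleeding (8.1.6.2.4): "The incidence of major bleeding related to the test device at discharge or 30 days";
- severe structural damage (8.1.6.2.5): "The incidence of severe damage to cardiac or other body structures related to the test device";
- infective endocarditis (8.1.6.2.6): "The incidence of device-related infective endocarditis at discharge or 30 days";
- thromboembolic events (8.1.6.2.7): "The incidence of thromboembolic events related to the test device".

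The endpoint lists in the synopsis and in sections 7.1.7.1 and 7.1.8 carry the same restriction, so it is the intended endpoint and not loose wording in the statistics section.

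Section 7.1.7.2.1 says who decides. Device-related serious adverse events are "events determined by the independent clinical event committee to be related, definitely related, or possibly related to the trial device". Blinding of this committee is not stated. Section 7.1.3, on measures against bias, covers randomisation, training and monitoring only.

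Two safety tests have no attribution filter: all-cause mortality (8.1.6.2.2) and the incidence of adverse events up to 5 years (8.1.6.2.8). Section 8.1.6.3 also tabulates adverse events and serious adverse events by severity, system organ class and preferred term. Section 7.1.7.2.2 provides for safety evaluation at every visit to 12 months and then "annually from 2 to 5 years postoperatively, recording all adverse events".

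**The concern.** Both arms have the same open operation and both receive a permanent ring. Whether one particular bleed, embolus or endocarditis was caused by the ring is often hard to decide for the individual patient. The protocol shows this difficulty itself: its list of surgical complications (6.5.2) and its list of device-related complications (6.5.3) contain the same 17 items, including thrombosis, endocarditis and bleeding from anticoagulation.

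Randomisation avoids the need for that judgement if every event meeting the definition is counted in both arms. A relatedness filter is applied after randomisation. If it works differently for a new ring and a long-marketed one, the compared rates differ from the true rates by a different factor in each arm. A real excess could then shrink, or an apparent one could arise, in the safety results that go into the registration report.

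The unfiltered outputs do not fill the gap. Mortality is only one of the harms. The any-event test pools everything over five years. The system organ class and preferred term tables do not apply the protocol's definitions: major bleeding, for example, is BARC type 3b or higher excluding type 4 (7.1.7.2.1), which a preferred-term count does not show.

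**Working it through.** **The plan's own figures.** The protocol gives no event rate, attribution rate or power for any safety endpoint, so there is no safety figure to reproduce. Section 8.2.1 gives 82 enrolled per group, from 75 evaluable for the primary test. The 75 reproduces: (1.960 + 0.842)² × 2 × 0.95 × 0.05 / 0.10² = 7.85 × 0.095 / 0.01 = 74.6, rounded up to 75. The present point does not depend on it; only the 82 per arm is used below.

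**Inputs.** From the protocol: 82 per arm (8.2.1), Fisher's exact test (8.1.6.2), two-sided 0.05 (8.3). Assumed: every event rate and attribution share.

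**Method.** If related events are a random fraction of all events, compared rate = true rate × share attributed. The probability of a significant result is the sum, over all pairs (i, j), of Bin(i; 82, p1) × Bin(j; 82, p2), counted where Fisher's p for i/82 v j/82 is at most 0.05.

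**Example.** True rate 15% in both arms, attribution 60% (test) v 20% (control): compared rates are 0.15 × 0.60 = 9% and 0.15 × 0.20 = 3%. The expected counts are 82 × 0.09 = 7.4 and 82 × 0.03 = 2.5, instead of 12.3 in each arm.

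| Assumed true rates, test v control | Attributed, test v control | Compared rates | Significant, all events | Significant, filtered |
|---|---|---|---|---|
| 15% v 15% | 60% v 20% | 9% v 3% | 3.0% | 24.1% |
| 10% v 10% | 60% v 20% | 6% v 2% | 2.9% | 11.6% |
| 5% v 5% | 60% v 20% | 3% v 1% | 1.7% | 1.7% |
| 20% v 5% | 50% v 50% | 10% v 2.5% | 80.5% | 38.6% |
| 20% v 5% | 30% v 30% | 6% v 1.5% | 80.5% | 15.6% |
| 20% v 5% | 25% v 50% | 5% v 2.5% | 80.5% | 4.5% |
| 25% v 15% | not random: filter removes shared surgical events | 10% v 1% | 28.8% | 63.4% |

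**Reading the table.** Rows 1 to 3 have no true difference. Uneven attribution creates false signals at 15% and 10%, but not at 5%, where Fisher's test is too conservative with so few events. Rows 4 to 6 have a real fourfold excess. Even-handed filtering lowers power, and uneven filtering can remove the signal. Row 7 goes the other way: with 15% surgical background in both arms and a 10-point excess from the ring, a filter that correctly discards the background more than doubles power.

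**The case against.** The case for leaving the plan alone has real weight.

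- **The plan is consistent.** Device-related endpoints are used throughout, and 8.1.6.2 analyses what the endpoint lists define. This stands: nothing is contradicted.
- **Attribution is safeguarded.** An independent committee decides, with a low threshold that admits possibly related events. This reduces the risk of distortion. It does not remove the dependence on a judgement made after randomisation.
- **Unfiltered information exists.** Mortality and any-adverse-event incidence are tested, all adverse events and serious adverse events are tabulated, and reoperation for tricuspid insufficiency is compared without a relatedness condition (8.1.6.1.4). This stands, but none of it compares the named harms under their own definitions.
- **All-event comparisons can be weak too.** At an assumed 10% v 5%, Fisher's test on all events has 15% power; at 5% v 2% it has 6%. Shared surgical events also dilute a device effect. This is why the device-related versions should stay.
- **Little depends on these p-values.** Trial success rests on the primary endpoint alone (8.5).

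A reader might go further than the documents allow in three ways. One is to infer that most events are thrown away; no attribution rate is given, and the threshold is low. Another is that these harms are lost from the randomised comparison altogether; they are recorded, tabulated and included in the pooled test. The third is that control-arm events can never count, because the wording refers to the test or trial device. That wording is unclear for the control arm, but 8.1.6.2 describes comparisons between groups, which presupposes counting in both.

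**Conclusion.** The point holds as a cheap improvement to the secondary safety analysis. As written, the protocol-defined harms other than all-cause death are compared between arms only after an attribution filter, applied by a committee whose blinding is not stated. What is established is the possibility of distortion, not its presence. Its size and direction cannot be read from the documents.

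On assumed rates, false significance ranges from no inflation (1.7% filtered and unfiltered, 5% in both arms) to 24% against 3% (15% in both arms, attribution 60% v 20%). Power can fall or rise. The falls assume that related events are a random fraction of all events; the rise assumes that the filter correctly removes surgical background. The primary non-inferiority conclusion is unaffected.

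**What to change.** In section 8.1.6.2, add a between-arm comparison of all events meeting the protocol definition, by arm and regardless of relatedness. Do this for cardiovascular death, major bleeding, severe structural damage, infective endocarditis, thromboembolic events and their composite, and for all serious adverse events. Give the rate in each arm, the difference and its confidence interval. Report these beside the existing device-related versions, which remain. State in 7.1.7.2.1 whether the committee is blinded to allocation.

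The cost is a few extra tables and applying the event definitions to all recorded events and not only to those judged related. No extra patients or visits are needed, because all adverse events are already collected. The downside is that all-event rates will be higher and diluted by surgical background, so the two sets of tables should be read together.

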
It is planned to issue a summary report to the China Food and Drug Administration after the 6-month follow-up of the subjects is completed. A one-year follow-up report will be issued after the 12-month follow-up is completed. Additionally, follow-up assessments will be performed at 2 years  $\pm$  30 days, 3 years  $\pm$  30 days, 4 years  $\pm$  30 days, and 5 years  $\pm$  30 days postoperatively to evaluate the long-term safety of the investigational product.

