## **7.2.6 Clinical Evaluation at 12 Months ( $\pm 30$ Days) Postoperatively**

**7.2.6.1** NYHA functional class.

**7.2.6.2** ECG, echocardiography (TTE).

**7.2.6.3** Record adverse events.

**7.2.6.4** Record antiplatelet or anticoagulant medications.

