## **7.2.7 Clinical Evaluation at 2, 3, 4, and 5 Years ( $\pm 30$ Days) Postoperatively**

**7.2.7.1** Telephone follow-up.

**7.2.7.2** Record adverse events.

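### The 5-year adverse-event comparison makes one proportion of a visit-based first year and telephone-only years 2 to 5, which can dilute a late difference between the arms

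*Protocol*

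**What the plan says.** **Analysis.** Protocol section 8.1.6.2.8 reads: "The incidence of adverse events from postoperative to 5-year follow-up will be compared", by a chi-square or Fisher test. It covers all adverse events, gives one window and does not divide it. The seven safety comparisons listed before it (8.1.6.2.1 to 8.1.6.2.7) all stop at month 12. The first, for example, concerns "The incidence of device-related serious adverse events (SAEs) at discharge or 30 days, 3 months, 6 months, and 12 months post-surgery". Item 8.1.6.2.8 is therefore the only between-group test in the protocol that extends to 5 years.

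**Ascertainment.** Sections 7.2.3 to 7.2.6 schedule four postoperative assessments up to month 12, each with transthoracic echocardiography, ECG, NYHA class and adverse-event recording. Section 7.2.7, although headed "Clinical Evaluation at 2, 3, 4, and 5 Years", lists only "Telephone follow-up" and adverse-event recording. The flowchart in 7.2.8 agrees: echo, ECG and NYHA class end at the 12-month visit.

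**Purpose.** Section 3.2 says that the follow-up in years 2 to 5 is "to evaluate the long-term safety of the investigational product". Section 7.1.7.2.2 puts both periods on one footing: "Safety evaluations will be conducted at discharge/30 days, 3 months, 6 months, 12 months, and annually from 2 to 5 years postoperatively", with all adverse events to be recorded.

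**The concern.** One proportion is formed over two periods in which events come to light in different ways. Section 6.5.3 lists recurrent regurgitation, valve stenosis and atrioventricular block among the device-related complications. When these are silent, no scheduled test can find them after month 12.

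A second effect needs no assumption about detection. In a proportion of patients with at least one event, a patient who had any adverse event in year 1 is already counted, so a later event in that patient changes nothing. Adverse events of any kind may be frequent in the year after cardiac surgery, and the more frequent they are, the fewer patients can still show a late difference.

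Both effects pull the observed difference towards zero. At stake is the long-term safety statement: a real late excess with the investigational ring could be reported as no difference over 5 years.

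**Working it through.** **The plan's own figures.** The protocol gives no adverse-event rate, detection share or power for this comparison. Its one sample-size calculation is for the primary endpoint and reproduces: (1.96 + 0.842)² × 2 × 0.95 × 0.05 / 0.10² = 74.6, so 75 per arm. That figure is not affected. From 8.2.1 I take 82 enrolled per arm. From the visit schedule, scheduled echo and ECG cover 12 of 60 months, or 20% of planned follow-up.

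**Model (every rate below is an assumption).** Let h1 be the year-1 hazard with full detection, h2 the annual hazard in years 2 to 5, and s the share of late events detected. Late events are taken as independent of year-1 events. Then:
- observed 5-year proportion = 1 − exp(−(h1 + 4·h2·s));
- late-period proportion = 1 − exp(−4·h2·s).

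If h1 is the same in both arms, the pooled difference equals exp(−h1) times the late-period difference. Power is the normal approximation for two proportions, two-sided 0.05, 82 per arm, no dropout.

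**Step 1: no difference between the arms.** With 5% a year in both arms and the same s, the difference is 0 for every s. The observed 5-year proportion is 22.1%, 18.1%, 13.9% and 9.5% at s = 1, 0.75, 0.5 and 0.25, against 22.1% true. The level is understated, but the comparison is not biased.

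**Step 2: late-only doubling, dilution by under-detection.** Take h1 = 0.05 in both arms, then h2 = 0.05 versus 0.10.

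| s | Pooled proportions | Difference (points) | Pooled power |
|---|---|---|---|
| 1 | 22.1% v 36.2% | 14.1 | 51% |
| 0.75 | 18.1% v 29.5% | 11.4 | 40% |
| 0.5 | 13.9% v 22.1% | 8.2 | 28% |
| 0.25 | 9.5% v 13.9% | 4.4 | 14% |

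**Step 3: same late doubling, full detection, dilution by year-1 events.** The late-period proportions are 1 − exp(−0.2) = 18.1% and 1 − exp(−0.4) = 33.0%, a difference of 14.8 points.

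| h1 | Patients with a year-1 event | Pooled difference (points) | Pooled power |
|---|---|---|---|
| 0.05 | 4.9% | 0.951 × 14.8 = 14.1 | 51% |
| 0.3 | 25.9% | 0.741 × 14.8 = 11.0 | 29% |
| 1.0 | 63.2% | 0.368 × 14.8 = 5.5 | 12% |

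A test of the late period alone does not depend on h1. Its power is 59% with 82 per arm, or 57% if 78 per arm are still in follow-up at month 12.

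**Step 4: what splitting does not recover.** With h1 = 0.05 and s = 0.5, the late-period difference is 18.1% − 9.5% = 8.6 points. Power is 36% with 82 per arm, against 28% pooled. The split removes the year-1 dilution but does not find events that were never detected.

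**The case against.** The strongest case on the other side has five parts.

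- **The schedule is identical in both arms.** This stands, as Step 1 shows. A reader might infer bias between the arms, but the protocol gives no ground for it.
- **The item covers all adverse events, not device harm.** This stands. A reader might infer that long-term device-harm rates must fall after month 12 by construction. The device-related comparisons end at month 12 and are not pooled with the telephone years. A cumulative incidence cannot fall, and a lower annual rate follows only if late detection is incomplete.
- **Ascertainment does not rest on scheduled contacts alone.** Section 13.1 requires every adverse event during the trial to be recorded, and section 13.3 sets a 24-hour report for serious ones. Death, reoperation, stroke, or a diagnosis made in routine care can be reported by telephone. This stands: s may be near 1 for many events, and the documents give no value.
- **First-year data are reported separately, and windows are SAP detail.** Sections 3.2 and 7.1.5.5 plan reporting at 6 and 12 months, so year 1 will be seen on its own, and the SAP, not shown here, may split the periods. This stands only in part. The protocol states a single pooled window for this test and plans no comparison for the period after month 12.
- **Restricting late events to those a telephone call can establish would lose data.** This stands. It would drop recorded events such as late endocarditis, against the all-event scope of 7.1.7.2.2. Such a restriction can only be supplementary.

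**Conclusion.** The point holds as a loss of sensitivity in one secondary safety comparison. Section 8.1.6.2.8 combines two ascertainment regimes, and lets year-1 events use up patients, in the only between-group test that reaches 5 years.

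The size cannot be fixed from the documents. Under an assumed late-only doubling from 5% to 10% a year with full detection, pooling costs 6 to 8 points of power when year-1 events are rare (51% against 57% to 59%). It costs far more when they are common (29% to 12% against the same 57% to 59%). Incomplete late detection takes more from either analysis.

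A reader might also infer that year 1 dominates the pooled figure. At a constant 5% a year with s = 0.5 it does not: 4.9 of 13.9 points, about 35%. It would if events cluster early or late detection is very poor, and the protocol shows neither.

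The primary endpoint, margin, alpha and sample size are unaffected.

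**What to change.** Reword 8.1.6.2.8 as follows:

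1. Compare adverse-event incidence separately for 0-12 months and for >12-60 months. The second counts new events among patients still in follow-up at month 12, whether or not they had an event in year 1.
2. Keep all recorded adverse events in both periods.
3. State that years 2 to 5 were ascertained by annual telephone contact and spontaneous reporting, without scheduled echo or ECG, and draw no trend across month 12.
4. If a 0-5-year comparison is kept, one limited to events a telephone contact can establish (for example death, reoperation, hospitalisation, stroke or embolism, major bleeding) may be added, as supplementary only.

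The cost is wording and one more secondary comparison, with no new visits or tests. The long-term safety statement becomes narrower, and the change does not recover silent late events.
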